#### Exploratory outcome measures

Uncertainty will be reported by estimating 95% confidence intervals for the mean value of costs and effectiveness in each group, and for the difference in mean value of costs and effectiveness between groups. Non-parametric bootstrap analysis will be carried out to estimate the sampling distribution of the ICER estimator in the cost-effectiveness plane (where each treatment is compared with information and advice) [51]. To reflect uncertainty in the threshold value for a QALY, cost-effectiveness acceptability curves will be computed, where the probability of cost-effectiveness is presented for different threshold values (from SEK 0 to 1,500,000). Cost-effectiveness acceptability curves will be computed based on parametric and non-parametric bootstrap methods using the net benefit approach [51]. Sensitivity analysis will also be carried out where the unit costs will be changed (±50%), and where QALYs, instead of being based on EQ-5D-3L, will be estimated based on SRH. In another sensitivity analysis, the indirect costs will be estimated based on number of hours absent from work during the past 7 days. The average number of hours absent from work during the first 3 months was assumed to be an average of the hours absent from work at baseline and at 3 months, whereas the average number hours absent from work during the other periods (4–6 months and 7–12 months) was calculated equivalently. To estimate the loss in production due to absence from work for the first 12 months, the average number of hours absent from work during each period will be multiplied by the average per hour value of labour production for a Swedish worker.

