In Sweden, patients with low back pain are often treated by either chiropractors or physiotherapists. Sometimes patients are treated by chiropractors and physiotherapists in collaboration. Besides providing general information and advice, these occupational groups usually recommend exercise (mostly recommended by physiotherapists) and manual therapies (mostly recommended by chiropractors) [7]. These treatment alternatives are also recommended in guidelines in different parts of the world [27]. As noted above, although a wide range of treatments exist for CLBP, the scientific basis to recommend the use of one treatment alternative over another is limited. There is, therefore, a need for well-designed clinical trials investigating both the effectiveness and cost-effectiveness of treatments for CLBP. Cost-effectiveness studies may provide valuable information on whether it is good value for money to use treatments and examinations provided by chiropractors and/or physiotherapists, in addition to only providing information and advice. Information both about the cost-effectiveness and effectiveness of treatments for CLBP is crucial for decisions aiming at improving the efficiency in the allocation of limited resources for the treatment of CLBP. The results from our study will improve the basis for health care decision-making and policy recommendations and should be considered when producing and updating evidence-based guidelines and recommendations on which treatment strategies to use for CLBP.

The aim of the study is to evaluate the effectiveness (back pain-related functional limitation, back pain intensity, general health, HRQoL, and working status), costs (medical costs and costs for production losses) and cost-effectiveness of chiropractic care and physiotherapy when added to information and advice in the treatment of patients with non-specific CLBP in Sweden.

Research questions:How do chiropractic care and physiotherapy, chiropractic care, or physiotherapy, when added to information and advice, impact outcomes (back pain-related functional limitation, back pain intensity, general health, HRQoL, and working status) as compared with only information and advice?Which (if any) of chiropractic care and physiotherapy, chiropractic care, or physiotherapy, when added to information and advice, is a cost-effective treatment strategy when compared to each other, and when compared with only information and advice?

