To estimate the number of QALYs for each treatment the quality-of-life values based on EQ-5D-3L will be used. The average number of QALYs during 12 months is calculated as the area under the curve during 12 months. A treatment is defined as cost-effective if the treatment is less costly while providing the same or better health outcomes, or if the added cost of the treatment is reasonable in comparison to the health outcomes obtained, in which case the incremental cost per gained QALY is estimated. An intervention is in the latter case defined as cost-effective if the cost per QALY gained is below or equal to a threshold value corresponding to how much society is willing to pay in order to gain a QALY. Different threshold values for a QALY have been used in cost-effectiveness studies and the value has usually been set to around US$50,000 (corresponding to approximately SEK 400,000 using the average exchange rate during 2016 of 1 US$ = SEK 8.6). However, Neumann et al. (2014) argue for using a threshold value of either US$100,000 or 150,000 for a QALY and that a threshold value of US$50,000 should be interpreted as a lower boundary [42]. If the threshold value of a QALY is derived from the literature on the value of a statistical life, even higher threshold values are derived (US$100,000–400,000) [42, 43]. In Sweden, the Swedish Transport Administration (STA) uses a value of a statistical life of SEK 24 million in cost-benefit analysis of road investments. Using this figure, a value per QALY gained of about SEK 950,000 can be derived (US$110,000). In our study, we define an intervention to be cost-effective if the cost per gained QALY is equal to or below SEK 900,000 (US$100,000).

The cost-effectiveness analysis will be reported in accordance with the Consolidated Health Economic Evaluation Reporting Standards (CHEERS) [44] and good research practices on how to conduct cost-effectiveness analysis alongside clinical trials [21]. Unit costs, data sources, and mean use of health care resources will be reported for each treatment. Mean costs for each treatment will be presented as well as incremental costs and effectiveness.

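### Research question 2 asks for cost-effectiveness between the active strategies, but the only comparator stated for the ICER is information and advice, and no incremental analysis across the four arms is stated

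*Protocol article*

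**What the plan says.** All references are to the protocol article.

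- **Background, research question 2.** It asks which, if any, of the three active strategies "is a cost-effective treatment strategy when compared to each other, and when compared with only information and advice".
- **Statistical analysis, Exploratory outcome measures, ICER.** The sampling distribution of the ICER is to be bootstrapped in the cost-effectiveness plane, "where each treatment is compared with information and advice".
- **Same section, intervals.** 95% confidence intervals are planned for mean costs and effectiveness in each group and "for the difference in mean value of costs and effectiveness between groups". They are not tied to one comparator, but they treat costs and effects separately.
- **Same section, curves.** "Cost-effectiveness acceptability curves will be computed based on parametric and non-parametric bootstrap methods using the net benefit approach". No comparator is given.
- **Costs and quality-adjusted life years (QALYs), decision rule.** A treatment counts as cost-effective if it costs less without a loss of health. Otherwise its incremental cost per QALY is set against a threshold: "we define an intervention to be cost-effective if the cost per gained QALY is equal to or below SEK 900,000". Neither part names a comparator.
- **Same section, reporting.** "Mean costs for each treatment will be presented as well as incremental costs and effectiveness". Again no comparator is named.

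**The concern.** Four randomised strategies give six pairwise contrasts. Three are against information and advice and three are between active arms. The question covers all six. The stated ICER comparison covers the first three.

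This matters because the strategies are alternatives: a guideline would choose one of them for a given patient. With more than two alternatives, the informative ICER for an arm is the one against the next-best arm that is not dominated. An ICER against a common reference averages in gains that a cheaper arm already delivers. A rule that judges each intervention singly against SEK 900,000 can then pass several arms without saying which is best value.

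The contrast between active arms is not a side issue here. The Background cites a UK trial-based evaluation in which manipulation alone was probably cost-effective compared with manipulation followed by exercise. That is close to this trial's contrast of chiropractic care with the combination. The Discussion intends the results for guidelines on which strategy to use.

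**Working it through.** **1. The document's own figure.** The threshold is SEK 900,000, given as equivalent to US$100,000. At the stated rate ("using the average exchange rate during 2016 of 1 US$ = SEK 8.6"), 100,000 × 8.6 = SEK 860,000, and 900,000 / 8.6 = US$104,651. The two amounts agree only after rounding. SEK 900,000 is used below; example A would also pass at 860,000.

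**2. Contrasts.** Four arms give 4 × 3 / 2 = 6 pairs. Of these, 3 involve information and advice and 3 are between active arms. A comparator for the ICER is stated for the first 3.

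**3. Mechanism, example A.** The article gives no costs or QALYs by arm, so all increments over information and advice are hypothetical. Net monetary benefit (NMB) = 900,000 × QALY gain − added cost.

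| | Added cost (SEK) | QALY gain | ICER against advice (SEK) | NMB (SEK) |
|---|---|---|---|---|
| Physiotherapy | 20,000 | 0.05 | 400,000 | 45,000 − 20,000 = 25,000 |
| Combination | 60,000 | 0.07 | 857,143 | 63,000 − 60,000 = 3,000 |

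Both pass against advice. Combination against physiotherapy: (60,000 − 20,000) / (0.07 − 0.05) = SEK 2,000,000 per QALY, more than twice the threshold.

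**4. Mechanism, example B (also hypothetical).**

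| | Added cost (SEK) | QALY gain | ICER against advice (SEK) | ICER against next cheaper arm (SEK) | NMB (SEK) |
|---|---|---|---|---|---|
| Physiotherapy | 10,000 | 0.03 | 333,333 | 333,333 | 17,000 |
| Chiropractic care | 25,000 | 0.04 | 625,000 | 15,000 / 0.01 = 1,500,000 | 11,000 |
| Combination | 40,000 | 0.05 | 800,000 | 15,000 / 0.01 = 1,500,000 | 5,000 |

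All three pass against advice. Only physiotherapy passes incrementally.

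**5. How easily several arms pass together.** The three active arms' increments were drawn independently from uniform distributions: QALY gain from 0 to 0.05 or 0.10, added cost from 0 to SEK 30,000 or 60,000. Two or more arms passed against advice in 32% to 93% of draws, depending on the ranges. Whenever two pass with unequal net benefit, at least one passing arm is not the best value. The percentages depend wholly on the assumed ranges.

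**6. Uncertainty.** Example B was simulated with 120 analysed per arm (150 × 0.8, the planned group size after 20% dropout). Assumed SDs were 0.15 QALY with SEK 60,000, and 0.20 QALY with SEK 100,000; costs and QALYs were drawn independently. For chiropractic care at SEK 900,000:
- probability of being cost-effective against advice: 72% and 66%;
- probability against physiotherapy: 38% and 41%;
- probability of being the best of the four: 28% in both.

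A curve whose comparator is not stated could be reporting any of these three quantities.

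**7. What can be recovered from the planned output.** Net benefit is additive. In example B, chiropractic care against physiotherapy is 900,000 × 0.01 − 15,000 = SEK −6,000 directly, and 11,000 − 17,000 = SEK −6,000 by way of advice. Group means therefore give the point contrast. Three separate planes against advice do not display the ICERs or the joint uncertainty between active arms.

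**The case against.** A reader might infer that the whole economic evaluation is confined to comparisons with information and advice, so that research question 2 cannot be answered. The article does not support that. The restriction qualifies only the sentence on the ICER bootstrap and the plane, and a plane needs some reference point. The between-group intervals, the acceptability curves and the incremental results are not restricted. As step 7 shows, the arms can be ranked by net benefit from their group means.

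A reader might also infer that the decision rule ignores dominance. It does not: its first part accepts a treatment that costs less without a loss of health. Since the rule names no comparator, it could be applied between active arms.

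Nor do the documents show that the combination will be the most costly arm. Costs include production losses, which the Background puts at about 85% of the total for chronic low back pain in primary care, and the amount of treatment is left to the provider. More treatment could be offset by better working status. The point does not depend on which arm costs most.

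Finally, these outcomes are labelled exploratory, the article commits to CHEERS and good research practice, and details of dominance are often left to an analysis plan. That explains missing detail. It does not explain a comparator that is stated and covers only half of the question. That question is one of two in the trial and the subject of the second planned paper.

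**Conclusion.** The point holds in this form. The only comparator stated for the ICER does not match the between-strategy half of research question 2. The comparator for the SEK 900,000 rule and for the acceptability curves is unspecified, and no incremental analysis across the four arms is stated. Applied against information and advice, the rule can call several alternatives cost-effective when one of them lies well above the threshold against the next-best arm.

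The size in this trial is unknown. The worked examples, the 32% to 93% range and the simulated probabilities all rest on assumed costs, QALYs and SDs, and they show only that the mechanism operates at plausible-looking values. The data to be collected can answer the question. What is missing is a stated analysis that does so, fixed before results are seen, so that the comparator is not chosen afterwards.

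**What to change.** In the analysis plan, and as a correction to the Exploratory outcome measures paragraph:

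1. State a full incremental analysis: order the four arms by mean cost, remove dominated and extendedly dominated arms, and compute each ICER against the next-best remaining arm.
2. Define the preferred strategy as the arm with the highest expected net monetary benefit at SEK 900,000, and state the comparator wherever the threshold rule is used.
3. Compute the acceptability curves for all four arms jointly from the same bootstrap replicates, so that the probabilities sum to 1 at each threshold value.
4. Keep the ICERs and planes against information and advice as supplementary results.

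The cost is a paragraph of wording and slightly more analysis work. It needs no new data and no change to the conduct of the trial.

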##### A measure of working status

The study participants will be asked to answer questions about current working status and number of hours absent from work due to illness during the past 7 days. For each participant, working status is defined as self-reported percentage of full-time work.

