#### Exploratory outcome measures

##### Costs and quality-adjusted life years (QALYs)

We will analyse the difference in costs during 12 months after the randomisation between the different treatment groups. Both direct and indirect costs will be estimated. Direct costs include costs for pharmaceuticals, health care visits, clinical examinations, and hospital days. Information about each participant’s resource consumption is collected by using a computer-based questionnaire. At each follow-up occasion (at baseline, and at 3, 6, and 12 months after baseline) the participant is asked to recall their resource consumption during the last 3 months (quantities of resource consumption is, e.g. number of prescriptions, number of visits to health care providers, number of clinical examinations, and number of hospital days). To estimate the direct costs the quantities of resource consumption is multiplied by the unit costs. Unit costs of pharmaceuticals are collected from the price database available at TLV and unit costs for health care visits will be based on prices in the Stockholm County Council for primary health care [37, 38]. Unit costs for clinical examinations and hospital days will be based on unit costs in the Stockholm County Council and in the southern part of Sweden (Region Skåne) [39].

The indirect costs refer to costs of changes in productivity (labour production) [40]. Data on changes in productivity while being at work (presenteeism) is not collected in the study. The working status of each participant, defined as the percentage of full-time work, was recorded at baseline and at 3, 6, and 12 months after baseline. The working status is estimated as the percentage of full-time work for each participant. The labour production value was estimated for the period from the first visit (at baseline) until 3 months, and for 4 to 6 months, and for 7 to 12 months. The average working status during the first of these periods (0–3 months) was assumed to be an average of the working status at baseline and 3 months. The average working status during the other periods (4–6 months and 7–12 months) was calculated equivalently. To estimate the value of production for the first 12 months the average working status during the first 12 months will be multiplied by the average value of labour production of a Swedish worker [40, 41].

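### The hours-absent sensitivity analysis turns 7-day absence figures into a 12-month production loss with no factor for the weeks in each period

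*Protocol article*

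**What the plan says.** The section on working status has participants report the "number of hours absent from work due to illness during the past 7 days". Under Statistical analysis, Exploratory outcome measures, one sensitivity analysis uses that item: "the indirect costs will be estimated based on number of hours absent from work during the past 7 days". The calculation is then set out in two steps.

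- Period value: the average for the first 3 months is "assumed to be an average of the hours absent from work at baseline and at 3 months", and the average for "the other periods (4–6 months and 7–12 months) was calculated equivalently".
- Costing: the aim is stated as "To estimate the loss in production due to absence from work for the first 12 months", and the rule is that "the average number of hours absent from work during each period will be multiplied by the average per hour value of labour production".

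The main analysis, under Costs and quality-adjusted life years (QALYs), averages the percentage of full-time work over the same three periods, after which "the average working status during the first 12 months will be multiplied by the average value of labour production of a Swedish worker".

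**The concern.** The mean of two 7-day counts is still a count per 7 days. Hours per week times kronor per hour gives kronor per week, yet the product is presented as a 12-month amount. No sentence in the article supplies the missing factor.

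The structure fits the main analysis, where the averaged quantity is a proportion of full-time work and a 12-month average proportion can be applied directly to a yearly production value. It does not carry over to a weekly count.

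This is the only planned analysis that costs reported hours of sickness absence. The Background cites earlier work in which production losses made up about 85% of the cost of chronic low back pain. If the rule were programmed as printed, the check could not test the main result as intended, and a shift in the cost per QALY could reflect a unit error rather than a different way of measuring lost work.

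**Working it through.** The article gives no production-loss figure, so there is none to reproduce. The check is one of units.

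**Inputs**

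- Recall window: 7 days at each occasion (A measure of working status).
- Occasions: baseline, 3, 6 and 12 months (Data collection).
- Periods: 0–3, 4–6 and 7–12 months, taken as 13, 13 and 26 weeks, total 52.
- Assumption not in the article: the three products are summed.

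**Formulas**

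Let a1, a2, a3 be the period means in hours per week.

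- Literal rule: L = a1 + a2 + a3
- Scaled to calendar time: S = 13·a1 + 13·a2 + 26·a3
- Understatement: S/L = 13 × (1 + s), where s = a3/(a1 + a2 + a3)

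**Constant absence**

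Here s = 1/3, so S/L = 13 × 4/3 = 52/3 = 17.3. With 4 hours a week, L = 12 hours and S = 52 × 4 = 208 hours.

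**Range**

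With s = 0 (no absence weight after 6 months) the factor is 13. With s = 1 (all of it in months 7–12) it is 26.

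**Illustrative trajectories** (assumed hours at 0/3/6/12 months)

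| Trajectory | a1, a2, a3 | L | S | S/L |
|---|---|---|---|---|
| 12/8/6/4 | 10, 7, 5 | 22 | 130 + 91 + 130 = 351 | 16.0 |
| 16/8/4/2 | 12, 6, 3 | 21 | 156 + 78 + 78 = 312 | 14.9 |
| 4/6/8/12 | 5, 7, 10 | 22 | 65 + 91 + 260 = 416 | 18.9 |

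**Weighting**

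Under the literal sum, months 7–12 get weight 1/3; by calendar time they should get 26/52 = 1/2. The error is therefore not a constant that could be divided out afterwards. If two arms followed the first and third trajectories, the literal rule would give 22 hours in each and no difference, whereas the scaled totals differ by 416 − 351 = 65 hours per person.

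**If the products were averaged instead of summed**

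The shortfall would be three times larger: 52-fold under constant absence, with a range of 39 to 78.

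**The case against.** The strongest reply is that the article is silent on the conversion rather than wrong. It never says that the weekly figure is multiplied once and unscaled. It names the quantity as hours during each period, it states a 12-month target, and a condensed article may leave the weeks factor to the full plan. The main analysis is equally brief: it does not say how its three unequal periods are weighted.

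Part of this stands. The full plan is not at hand and may contain the conversion, and nothing shows that the analysis will be run without it. The size also depends on how the periods are combined and on the course of absence, and the article gives neither.

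The whole-period reading does not fit the text, however. The preceding sentence defines the period quantity as the mean of the values at the two bounding occasions, and the only absence value recorded is the 7-day one. Since the article writes the rule out step by step, the gap lies in what is stated. The brevity of the main analysis is a different matter, because a proportion needs no conversion from a recall week.

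A reader might go further and infer that the trial's production losses will be understated 17-fold, that indirect costs will all but disappear, or that the check will falsely reassure. The documents do not support this. The figure of 17.3 is one case within a range and rests on assumptions. The main indirect-cost estimate does not use hours absent. A loss more than ten times too small might well be noticed beside the main estimate.

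**Conclusion.** The concern holds in a limited form. Followed as printed, the rule is dimensionally incomplete: it prices weekly absence and labels the result a 12-month loss. If the three products are summed, about 3 of 52 weeks are costed. The loss is then 17.3-fold too low under constant absence and between 13-fold and 26-fold too low otherwise, with the longest period underweighted. That range applies to one arm's total; a between-arm difference can be distorted in other ways when absence follows different courses in the arms.

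The reach is small: one sensitivity analysis of an exploratory outcome. The main indirect-cost analysis, the QALY calculation and the primary analysis of the Oswestry Disability Index are untouched.

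**What to change.** Replace the costing sentence under Statistical analysis, Exploratory outcome measures, with an explicit formula:

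production loss over 12 months = hourly value × [13 × mean weekly hours absent (0–3 months) + 13 × mean weekly hours absent (4–6 months) + 26 × mean weekly hours absent (7–12 months)].

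This supplies the weeks factor, the weighting of the third period and the rule for combining periods. If the full analysis plan already contains the conversion, it is enough to bring the published wording into line with it. The cost is one line of text; data collection does not change.
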